**Research Protocol**

**INTRODUCTION**

With the introduction of cervical cancer screening since 1920s, the incidence and mortality rates of cervical cancer has decreased by 60-90%.[1] However, cervical cancer is still the second most common female cancer worldwide and it remains to be a global burden.[2] In Hong Kong, cervical cancer was the fifth commonest female cancer and there were 459 new cases and 133 mortality cases in 2006.[3] Conventional and liquid-based cytology is the traditional screening tool. However, its accuracy is limited by several factors such as the patients’ estrogen status, sampling techniques and variation in the interpretation of cytopathologists. The sensitivity and specificity of cytology testing were estimated to range from 30 – 90% and from 70 – 100% respectively.[4-9] Attempts have been made to look for new screening tools including human papillomavirus (HPV) testing, cervicography, visual inspection with acetic acid (VIA) and with Lugol’s iodine (VILI).

HPV is the causative agent of cervical cancer.[10-11] This strong relationship has attracted attention to evaluate the efficacy of applying HPV testing in the screening for cervical cancer and its pre-invasive lesions. Currently, HPV testing is commonly used in triaging patients with atypical squamous cells of undetermined significance (ASCUS) for colposcopy and biopsy.[12-15] Recent research has focused on the comparison of HPV testing with conventional cytology testing in primary screening. Despite the heterogeneity of the study designs and follow-up methods, randomized controlled trials and meta-analyses have shown that the sensitivity of HPV testing for the detection of cervical intraepithelial neoplasia (CIN) grade 2 or higher is above 90% in general, being 25 - 30% higher than that of cytology testing with a relative sensitivity ranging between 1.16 and 3.50.[16-27] Moreover, the implementation of HPV testing led to earlier detection of CIN 2 or worse and might potentially lengthen the screening interval to up to 5 or 6 years.[23, 28] Nevertheless, the specificity of HPV DNA test was 67 - 94%, being about 6% less than that of cervical cytology. The positive predictive value (PPV) was also lower, with the relative PPV being 0.58 – 0.99 depending on the age-group and the cutoff value of the viral load used.[23, 28]

On the other hand, one study demonstrated that the use of HPV and cytology testings in primary screening increased the sensitivity of detecting CIN 3 or cancer by 35% (95% confidence interval [CI] 15 – 60%) with an insignificant decrease of PPV (relative PPV 0.76, 95% CI 0.52 – 1.10).[27] Meanwhile, other similar studies detected a substantial reduction in the PPV (relative PPV 0.55, 95% CI 0.37 – 0.82 for women aged 25 – 34; relative PPV 0.40, 95% CI 0.23 – 0.66 for women aged 35 - 60).[29, 30] A recent cohort study in Taiwan showed that the addition of HPV testing to cytology testing improved the sensitivity by 15.3% with a decrease of specificity by 9.6%, while the addition of conventional smear to primary high-risk HPV testing improved the sensitivity by 12.5% with a decrease of specificity by 0.5%.[31] The controversy of these studies makes it difficult to determine whether co-testing is cost-effective, and the complexity of different screening and follow-up strategies also fail to identify the best approach. In addition, there is no data on the performance of cytology and HPV testing in the local Chinese population. Therefore, our objective is to conduct a prospective study to compare the use of concomitant HPV-cytology testing with conventional cytology testing in primary cervical screening for the detection of high grade CIN among Hong Kong Chinese women.

**METHODOLOGY**

**Study Aim**

To compare HPV-cytology co-testing with cytology testing in primary cervical screening for the detection of high grade cervical intraepithelial neoplasia (CIN2 or higher) among Hong Kong Chinese women aged 30 years or above.

**Subjects**

*Inclusion criteria*

- Ethnic Chinese women aged 30 to 60 years who have completed a written consent
- Women who have not attended screening for the past 3 years or more will be given priority

*Exclusion criteria*

- Currently pregnant
- Without a cervix
- Congenital abnormalities of the lower genital tract
- Previous history of invasive cervical cancer
- Who has been followed-up or treated for an abnormal cytology result in the past 12 months
- Who are unable to provide consent

*Recruitment*

Women attending the women’s health clinics of the Family Planning Association of Hong Kong or the Lady Helen Woo Women’s Diagnostic and Treatment Centre for routine cervical cancer screening will be recruited. Eligible women will be given an information sheet containing details on cervical cancer and HPV testing and about the present study.(App. A & B) Women who are interested to participate will be asked to complete an informed consent (App. A & B) and a self-administered questionnaire (App. C & D) to collect baseline data on personal demographics, past screening history, behavioural risk factors for cervical cancer and other information related to ancillary cost-effectiveness study and psychosocial studies.

**Study Design**

This is a prospective randomized controlled trial to study the effect of HPV-cytology co-testing as a primary screening strategy for women aged 30 years or above. Each consented participant will be randomized on a 1:1 ratio into one of two arms: Cytology arm (control) or cytology plus HPV testing arm (intervention). Participants will be followed for two rounds of screening or until the occurrence of high grade CIN, whichever takes place first. Cytology testing, HPV testing and histological studies of biopsies will be conducted by the laboratories of the University of Hong Kong. Colposcopy and biopsy, when indicated, will be performed by the colposcopists at the colposcopy clinic in Queen Mary Hospital or at the Lady Helen Woo Women’s Diagnostic and Treatment Centre. All final test reports will be reviewed and signed by the senior pathologists.

***Control arm***

The index test for participants in the control arm will be conventional cytology testing. HPV testing will also be administered. ,HPV results will not be revealed to the participant or healthcare professionals who are involved in the direct care of the participant except in the case of reflex HPV testing for borderline cytology results. Participants will be managed based on their cytology results according to the current practice of the involved clinics and the Hong Kong College of Obstetricians and Gynaecologists Guidelines. (Fig. 1) Colposcopy will be offered in the following conditions: (1) any cytologic abnormalities greater than ASCUS, (2) ASCUS and HPV positive, or (3) two consecutive ASCUS results. In addition, a random 5% of participants with negative cytology results will be invited to attend colposcopy at baseline at the Lady Helen Woo Women’s Diagnostic and Treatment Centre.  Post colposcopy management of participants is shown in Fig. 2. Participation in the study will be terminated at a diagnosis of CIN 2 or greater.

***Intervention arm***

The index test in the intervention arm will be concomitant cytology testing and HPV testing. Participants will be managed based on both their cytology and HPV results in accordance with the routine practice of the involved clinics, the Hong Kong College of Obstetricians and Gynaecologists Guidelines and expert opinion on the management following a positive HPV testing result. (Fig. 3) Participants who are HPV negative with borderline cytology at baseline will be re-tested in 12 months by cytology and HPV testings. For this study, HPV positivity is defined as the presence of one or more high-risk HPV subtypes. Colposcopy will be offered in the following conditions: (1) any cytologic abnormalities greater than ASCUS regardless of the HPV result or (2) two consecutive ASCUS results regardless of the HPV results or (3) HPV positivity. Post colposcopy management of participants is shown in Fig. 4. Participation in the study will be terminated at a diagnosis of CIN 2 or greater.

***Randomization***

A computer-generated block randomization algorithm with randomly varied block size will be used to randomize participants 1:1 into one of the two arms. Randomization will be carried out away from the recruitment sites at the central study base at the Department of O&G of the University of Hong Kong. Each cervical sample will be assigned a study ID at the recruitment site. Arm allocation information corresponding to the study ID of individual sample will be revealed to the processing laboratory.

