***Blinding***

Participants and recruitment staff will be blinded to the arm allocation at recruitment. Participants will be informed of their cytology and/or HPV results if necessary for subsequent follow-up. Cytology testing and HPV testing will be conducted by two separate teams of laboratory staff and they will be blinded to each other’s test results. Colposcopists will be blinded to the cytology and HPV results.

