***Cytology testing***

The labeled samples will be sent to the Cervical Cytology Laboratory, the University of Hong Kong and processed using TP 2000 Processors.[32] The specimen adequacy and the cytological features in these slides were then evaluated by the cytotechnologists using the Bethesda System.[36] Cytologic abnormalities including atypical squamous cells of undetermined significance (ASC-US) [33], atypical squamous cells cannot exclude a high-grade lesion (ASC-H), atypical glandular cells of undetermined significance (AGUS), low-grade squamous intraepithelial lesion (LSIL), high-grade squamous intraepithelial lesion (HSIL), and cancer were reported by pathologists.

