***HPV testing***

Reflex HPV DNA testing will be performed by the laboratory of the Department of Pathology in case of a borderline cytology result at baseline for the control group. Other HPV DNA testing and HPV genotyping will be performed by the laboratory of the Department of O&G.

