***Cervical Biopsies Reporting***

The cervical biopsy specimens and the biopsy request will be sent to the Cervical Screening Laboratory. After specimen identification and labeling, the specimens and forms with accession number will be transferred to the Histopathology Laboratory, the University of Hong Kong. The tissue will undergo procedures to produce thin sections for microscopic examinations, inlcuding tissue processing, embedding, microtome sectioning, and Haematoxylin and Eosin staining.

The pathologists on duty may be requested to perform macroscopic description and cut up for bigger specimens such as loop excision. After tissue processing, histology slides and the forms are then returned to the office of Cervical Screening Laboratory for distribution to pathologists on duty. The macroscopic and microscopic descriptions as well as diagnosis are entered into the same laboratory information system.

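### Each sample's arm is revealed to the processing laboratory, no cytology or biopsy reader is stated to be masked to arm, and control-arm ASCUS triage uses its own HPV laboratory

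*Protocol*

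**What the plan says.** All references are to the protocol.

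- **Randomization.** Allocation is generated at the central study base, away from the recruitment sites. Then: "Arm allocation information corresponding to the study ID of individual sample will be revealed to the processing laboratory".
- **Cytology testing.** "The labeled samples will be sent to the Cervical Cytology Laboratory, the University of Hong Kong and processed using TP 2000 Processors". The slides are "evaluated by the cytotechnologists using the Bethesda System", and pathologists report the abnormalities.
- **Blinding.** "Participants and recruitment staff will be blinded to the arm allocation at recruitment". For the laboratories: "Cytology testing and HPV testing will be conducted by two separate teams of laboratory staff", each masked to the other's results. For colposcopy: "Colposcopists will be blinded to the cytology and HPV results". Arm is mentioned only for participants and recruitment staff. Biopsy readers are not mentioned.
- **HPV testing.** "Reflex HPV DNA testing will be performed by the laboratory of the Department of Pathology" when baseline cytology is borderline in the control group. All other HPV testing goes to the Department of O&G. No assay is named for either laboratory, and no comparison between them is described.
- **Control arm and Intervention arm.** Controls reach colposcopy through a cytology call above ASCUS, ASCUS with a positive HPV test, two consecutive ASCUS results, or the random 5% sample of cytology-negative women. Intervention women reach it through the same cytology routes or any positive HPV test.
- **Outcome Measures.** The primary outcome is histological CIN2, CIN3 or cancer, diagnosed by biopsy.

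**The concern.** Normal versus ASCUS and CIN1 versus CIN2 are judgement calls. If the person making the call knows the arm, the threshold can move with the arm. Randomization does not balance that, and the planned chi-square comparison cannot remove it.

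The cytology call matters most in controls. A control woman read as normal is not referred at baseline unless she falls in the 5% sample, whereas an HPV-positive intervention woman is referred whatever her slide shows. A reader who knows the arm therefore knows when the slide is almost the only gate. The same call also decides which controls count as cytology-normal in the second-round comparison.

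The HPV laboratory is a separate matter. Women with the same baseline finding, ASCUS, are triaged on one laboratory's HPV result in controls and on another's in the intervention arm. Any difference between the laboratories would be counted as a difference between strategies.

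**Working it through.** **1. Does the arm reach the readers?** Randomization sends the code to a processing laboratory that it does not name. Cytology testing is the only section that describes the processing of cervical samples, and it names the Cervical Cytology Laboratory, where the slides are then read. No sentence restricts the code to staff who do not read. Exposure of readers is thus a likely consequence of the text, but it is not stated.

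**2. Does the Blinding section close the gap?**

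| Group | Stated masking to results | Stated masking to arm |
|---|---|---|
| Participants, recruitment staff | not the subject of the statement | yes, at recruitment |
| Cytology team | yes, to HPV results | none |
| HPV team | yes, to cytology results | none |
| Colposcopists | yes, to both | none |
| Biopsy readers | none | none |

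The masking to results also sits badly with the reflex pathway. A reflex request to the Pathology laboratory itself shows that the cytology was borderline. Because only control samples take that route, it shows the arm too.

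**3. The plan's own sample size, as background.** The protocol gives 12000 from 1.2% prevalence, a 25-point difference in sensitivity, 80% power, two-sided 5% and 10% loss, but no base sensitivity. Assuming 50% v 75%, the two-proportion formula gives

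[1.96 x sqrt(2 x 0.625 x 0.375) + 0.842 x sqrt(0.25 + 0.1875)]² / 0.25² = 57.7,

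or 66 cases per arm with continuity correction. Then 66 / 0.012 = 5500, 5500 / 0.9 = 6112 per arm, and 12,224 in total, within 2% of the stated figure. Other assumed bases give other totals. Nothing in this point disputes the 12000.

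**4. How many cases carry the comparison?**

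- Per arm: 6000 x 0.012 = 72 women with CIN2+; after 10% loss, 5400 x 0.012 = 64.8.
- Expected difference in detected cases: 72 x 0.25 = 18; after loss, 64.8 x 0.25 = 16.2.

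**5. Illustration only, with assumed shifts.** If arm-aware reading moved control-arm detection by s, the difference would move by 64.8 x s:

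- s = 5 points: 3.2 cases, or 5/25 = 20% of the expected difference.
- s = 10 points: 6.5 cases, or 40%.

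The protocol offers no value for s and no sign.

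**6. Reach of the second laboratory.** Fig. 1 expects 261 control women with ASCUS, 261/6000 = 4.35% of the arm. Fig. 3 expects 130 HPV-negative women with ASCUS in the intervention arm. If ASCUS is equally frequent there, 261 − 130 = 131, about half, would be HPV-positive. In controls, then, the HPV result would decide immediate referral for a group of about 261 in which the result could easily go either way. The second laboratory touches no one else.

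**The case against.** Several parts of the opposing case stand.

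- **The laboratory side has a reason to know the arm.** Reflex testing at Pathology applies to controls only, so someone must pick out control ASCUS samples. A reader might infer that the disclosure serves no purpose; as the workflow is written, that is wrong. It explains why the code is sent, but not why slide readers should have it.
- **Histology rests on silence.** A reader might infer that biopsy readers see the arm because reports are "entered into the same laboratory information system". That sentence says where descriptions and diagnoses are recorded; nothing says the system holds the allocation. Study Design also has senior pathologists review and sign all final reports. This is a safeguard on grading, though not masking.
- **A ready-made same-laboratory result is not established.** A reader might infer that every control woman with ASCUS already has an O&G result, so that the reflex test is a duplicate. Controls do receive HPV testing, but the protocol does not say when it is run, and its wording allows the reflex test to be that woman's baseline HPV test.
- **Separate reflex testing may be deliberate.** The control arm follows current clinic practice. With no assay named, a difference in performance between the laboratories is possible but not shown.
- **Other features limit the bias.** Colposcopists are masked to both results, every quadrant is biopsied, and endocervical curettage is done in all cases. In the intervention arm, arm-aware cytology can change baseline referral only among HPV-negative women. HPV-negative controls with ASCUS are retested at one year.

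None of this supplies a statement that cytology or biopsy readers are masked to arm, and Randomization actively provides for disclosure.

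**Conclusion.** The point holds in a limited form. The protocol discloses each sample's arm to a laboratory that appears to be the one reading the cytology, and it states no masking to arm for cytology or biopsy readers. It also ties the HPV laboratory to the arm for baseline ASCUS triage. Readings that lead to the primary outcome, or constitute it, could therefore differ by arm.

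This rests on one inference, that the processing laboratory is the Cervical Cytology Laboratory, and on the absence of any restriction on who there sees the code. It does not show that readers are in fact told the arm, that grading is biased, or that the two HPV laboratories disagree.

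Only the expected difference of about 18 CIN2+ cases (about 16 after loss) follows from the stated assumptions. A reader might go on to claim that a given number of biopsies would be misgraded or women misdirected; the documents support no such figure. The weakness is worth removing because the comparison rests on few cases and the repair is cheap.

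**What to change.** - **Randomization and Blinding.** State that the allocation code stays at the central study base, or with named laboratory staff who do not read slides. Those staff trigger the control reflex test and govern the release of control HPV results. State that cytotechnologists, reporting pathologists, HPV staff and biopsy readers are masked to arm.
- **HPV testing.** Use the same laboratory and assay for the HPV result in women with ASCUS in both arms where turnaround allows. This has to be confirmed, since the timing of the concealed control test is not given. It would also stop a reflex request from revealing the arm. If two laboratories must remain, report concordance between them and acknowledge that Pathology's HPV staff can infer the arm.

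The referral rules and the sample size are unchanged. The cost is a change in result routing and request handling and, with one laboratory, possible dependence on its turnaround for control triage. No saving in tests should be assumed.

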***Blinding***

Participants and recruitment staff will be blinded to the arm allocation at recruitment. Participants will be informed of their cytology and/or HPV results if necessary for subsequent follow-up. Cytology testing and HPV testing will be conducted by two separate teams of laboratory staff and they will be blinded to each other’s test results. Colposcopists will be blinded to the cytology and HPV results.

***Sample Collection***

At the recruitment clinics, the liquid based cervical cytology samples will be collected by PapetteTM collection devices, a broom-type sampling device and then rinsed directly into the PreservCyt vial. Women attending these clinics can be considered to be representing the Hong Kong screening population since the prevalence of low-grade and more severe SIL was less than 5%.[32, 34, 35]

***Cytology testing***

The labeled samples will be sent to the Cervical Cytology Laboratory, the University of Hong Kong and processed using TP 2000 Processors.[32] The specimen adequacy and the cytological features in these slides were then evaluated by the cytotechnologists using the Bethesda System.[36] Cytologic abnormalities including atypical squamous cells of undetermined significance (ASC-US) [33], atypical squamous cells cannot exclude a high-grade lesion (ASC-H), atypical glandular cells of undetermined significance (AGUS), low-grade squamous intraepithelial lesion (LSIL), high-grade squamous intraepithelial lesion (HSIL), and cancer were reported by pathologists.

***HPV testing***

Reflex HPV DNA testing will be performed by the laboratory of the Department of Pathology in case of a borderline cytology result at baseline for the control group. Other HPV DNA testing and HPV genotyping will be performed by the laboratory of the Department of O&G.

***Colposcopy and biopsy***

Colposcopy is performed using the Olympus Optical System. A speculum would be inserted into the vagina to expose the cervix. The cervix will be cleaned with normal saline and inspected under the colposcope with different magnifications. The cervix will then be applied with 3% acetic acid and be inspected with the colposcope in different magnifications. Acetowhite areas as well as abnormal vascular patterns will be noted during the examination. Lugol’s Iodine will be applied as an adjunct for the colposcopy examination. Cervical biopsies will be taken from the most suspicious areas in each quadrant of the cervix. If no abnormality was found at a particular quadrant, a random biopsy will be taken so that, at least one cervical biopsy will be taken from each quadrant. Endocervical curettage would be performed in all the cases. After the examination of the cervix, the vagina will be inspected. Vaginal biopsy will be taken only if lesions are identified. Haemostasis after cervical biopsy will be achieved using the Monsel’s solution. Additional methods like Silver Nitrate sticks or vaginal packing with the gauze roll will be used when necessary.

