**Duration of study**

Subject recruitment will take two years and a minimum of five years will be required to complete the second round of screening for all participants. Another year will be required for the completion of all reports, data entry and cleaning, statistical analysis and writing up of final report. The whole duration of the study is estimated to last from eight to ten years.

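### Curettage and quadrant biopsies are required at every colposcopy, with no exception for a pregnancy that begins after entry

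*Protocol*

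**What the plan says.** The Colposcopy and biopsy section sets one sampling rule for every colposcopy. Biopsies come from the most suspicious area of each quadrant, or at random where a quadrant looks normal, so that "at least one cervical biopsy will be taken from each quadrant". It then adds: "Endocervical curettage would be performed in all the cases". No exception is attached to either requirement.

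Under Subjects, the exclusion criteria list "Currently pregnant". This is the only mention of pregnancy in the visible protocol. The inclusion criterion is "Ethnic Chinese women aged 30 to 60 years".

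Study Design ends follow-up after the second screening round or at high-grade CIN. Pregnancy is not among the reasons for stopping. Under Duration of study, "a minimum of five years will be required to complete the second round of screening for all participants".

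**The concern.** An exclusion at entry settles pregnancy status on the day of recruitment and no later. The trial then follows women for years, many of them possibly of childbearing age, and sends some to further colposcopies. The sampling rule applies to each of these in the same way, with no pregnancy check, no deferral and no reduced procedure.

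What is at stake is the safety of the occasional participant who conceives between entry and a later colposcopy. The random biopsies matter most here, because they are taken from tissue that looks normal. The point concerns a rule that is stated universally. It is a clinical procedure, so a statistical analysis plan would not be expected to supply the exception.

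**Working it through.** The protocol gives no figure to reproduce, so the check sets the sampling rule beside each point at which a colposcopy can occur.

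**Step 1: is the rule conditional?** The same section uses conditions where the authors wanted them: vaginal biopsy depends on a lesion being present, and extra haemostasis depends on need. Curettage and quadrant biopsies carry no condition.

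**Step 2: when can colposcopy occur after entry?**

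| Source | Arm | Time | Trigger |
|---|---|---|---|
| Fig. 1 | Control | 1 year | ASCUS or worse at the repeat smear after ASCUS with negative HPV |
| Fig. 3 | Intervention | 1 year | HPV positive, or ASCUS or worse, at the re-test |
| Fig. 2 | Control | 6 months after first colposcopy | HSIL |
| Fig. 2 | Control | 1 year after | ASCUS or worse |
| Fig. 4 | Intervention | 6 months after | HSIL |
| Fig. 4 | Intervention | 1 year after | HPV positive or abnormal cytology |
| Fig. 4 | Intervention | 2 years after | HPV positive or abnormal cytology |

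The Intervention arm section confirms the 1-year re-test: "Participants who are HPV negative with borderline cytology at baseline will be re-tested in 12 months by cytology and HPV testings". In controls the post-colposcopy smears run to 1.5 years, so the 2-year time point belongs to the intervention arm only. Later screening smears are scheduled at 3 and 4 years (Figs. 1 and 3), and at 4.5 and 5 years after a first colposcopy (Figs. 2 and 4). Colposcopy can follow from these too, since the colposcopy conditions in the two arm sections are not confined to baseline.

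**Step 3: does the entry exclusion cover these?** No. Each time point in the table is at least 6 months after entry or after a first colposcopy. The exclusion does offer some cover for baseline colposcopies, including those of the random 5% of cytology-negative controls, who are invited at baseline. Exposure there is small.

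**Step 4: does other text supply the exception?** Controls are managed "according to the current practice of the involved clinics and the Hong Kong College of Obstetricians and Gynaecologists Guidelines", and intervention participants "in accordance with the routine practice of the involved clinics", together with the same college's guidelines and expert opinion. Both clauses concern what is done on a test result. How a colposcopy is performed is set in the Colposcopy and biopsy section. The figure legends define the abbreviation Bx as colposcopy with or without biopsy. That sits awkwardly with mandatory quadrant biopsies, and it is silent on curettage and on pregnancy.

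**Step 5: can the number affected be derived?** No. It would need the number of colposcopies after entry and the proportion of those women who are pregnant at the time. The protocol gives neither, and it gives no age distribution within 30 to 60.

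**The case against.** The strongest reply is that the sentence is being read too literally. The surrounding text defines sampling by what the colposcopist sees, so curettage in every case most naturally means whether or not a lesion is visible. Uniform sampling also has a design purpose: the primary outcome is histological, and accuracy is to be calculated from biopsy data. The procedure is done by colposcopists at named specialist clinics, who may well make the exception unprompted. The appendices with the information sheet and consent form are not shown and could contain a pregnancy instruction. Finally, no part of the protocol says that curettage or random biopsy is unsafe in pregnancy, or why pregnancy is excluded.

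Most of this stands as a limit on severity. The clinical premise is an assumption and has to be labelled as one. The claim that no exception exists can be made only for the visible text. But if the narrower meaning was intended, the wording does not say it, and recording it takes one sentence.

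A reader might infer three stronger things that the documents do not support:

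- **That the protocol contradicts itself.** It does not. Eligibility at entry and the sampling procedure are separate rules, and they do not conflict.
- **That the printed pathway counts measure the exposure.** Fig. 3 shows 240 + 275 = 515 HPV-positive intervention women going to baseline colposcopy, and 130 due the 1-year re-test. Fig. 1 shows 261 controls with ASCUS, 145 with worse than ASCUS, and 277 in the random 5%. These are baseline group sizes. They count neither later colposcopies nor pregnancies.
- **That the trial's comparison is affected.** Nothing here bears on power, on the analysis set or on the primary outcome comparison.

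**Conclusion.** The point holds as a minor participant-safety matter, worth considering because it is cheap to put right. As written, the sampling rule would apply to a woman who conceived after entry, and no visible text exempts her. The number of women affected cannot be estimated and is probably small.

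The conclusion rests on two assumptions: that routine curettage and random biopsies should be avoided in pregnancy, taken as ordinary clinical caution, and that the appendices not shown do not already deal with it.

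**What to change.** Amend the Colposcopy and biopsy section so that curettage and random quadrant biopsies are done in all cases except in pregnancy. Add a question about pregnancy before each colposcopy. In a pregnant participant, defer the omitted sampling until after the pregnancy and leave any directed biopsy to the colposcopist's judgement. If the present sentence was meant to say that curettage does not depend on seeing a lesion, say that as well.

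No change to the analysis population is needed, because Data analysis already follows the intention-to-treat principle. The cost is an amendment to one section, one question per colposcopy visit, and a few histology results that arrive late or are incomplete.
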